### Safety monitoring and adverse events

3.12

Participants will be continuously monitored during each virtual reality session for potential VR-related adverse effects, including dizziness, nausea, headache, visual discomfort, eye strain, fatigue, and disorientation.

Before each VR session, participants will be asked about any physical discomfort that might affect their participation. During the intervention, trained researchers will continuously observe participants for signs of cybersickness or other adverse reactions. Immediately after each session, participants will be asked about the presence and severity of any VR-related symptoms using a structured symptom checklist and open-ended questions.

All adverse events will be recorded in a standardized case report form, including symptom type, onset time, duration, severity, actions taken, and outcome.

A VR session will be suspended or terminated if the participant requests to stop, reports moderate-to-severe discomfort (e.g., dizziness, nausea, headache, visual disturbances, or disorientation), or if the supervising researcher determines that continued participation may compromise safety. Participants who experience persistent or recurrent adverse reactions will be referred for clinical evaluation, and their continued participation in the intervention will be jointly reviewed by the study director and the attending physician.

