#### Intervention group

3.6.2

Participants in the intervention group will receive a VR-based intervention in addition to usual care. The intervention will be delivered over a period of 4 weeks, with three sessions per week, and each session lasting approximately 25 min.

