### Safety monitoring and adverse events

4.3

All adverse events (AEs) and serious adverse events (SAEs) will be recorded from enrolment through the follow-up period. Participants will be asked at each visit about any discomfort or unexpected symptoms. AEs will be assessed for severity, causality, and expectedness. SAEs will be reported to the ethics committees and the sponsor within 24 h. The principal investigator is responsible for managing AEs and ensuring participant safety. No independent data monitoring committee was established, as the trial involves a low-risk, short-term intervention and is monitored jointly by the investigators and the institutional ethics committees.

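### Study symptom enquiry is more frequent and more structured in the VR arm, so any by-arm count of non-serious symptoms is expected to be higher there even if VR does no harm

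*Protocol article*

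**What the plan says.** Section 3.6.2 sets the VR programme as "delivered over a period of 4 weeks, with three sessions per week". Only the intervention arm attends these sessions.

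Section 3.12 attaches three layers of symptom ascertainment to each session:

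- before: "Before each VR session, participants will be asked about any physical discomfort that might affect their participation";
- during: "During the intervention, trained researchers will continuously observe participants for signs of cybersickness or other adverse reactions";
- after: "Immediately after each session, participants will be asked about the presence and severity of any VR-related symptoms using a structured symptom checklist", with open-ended questions as well.

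The symptoms looked for are listed as "including dizziness, nausea, headache, visual discomfort, eye strain, fatigue, and disorientation".

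For the trial as a whole, Section 4.3 states "All adverse events (AEs) and serious adverse events (SAEs) will be recorded from enrolment through the follow-up period", and the enquiry that covers both arms is "Participants will be asked at each visit about any discomfort or unexpected symptoms". What counts as a visit is not defined there. Table 1 has no assessment between T0 and T1. Section 3.12 puts all adverse events on one standardized form. Its listed items include type, onset time and severity, but not how the event came to light.

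Section 3.6.1 adds that both arms receive the same inpatient care, including ward symptom monitoring and safety assessments.

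**The concern.** Several of the listed symptoms (headache, nausea, dizziness, fatigue) are non-specific and can occur without VR. Both arms are also on psychiatric medication (Sections 3.3.1 and 3.6.1). The more often and the more specifically people are asked, the more of these background symptoms are written down. Here one arm is asked before and after every session, with a checklist afterwards, while the other gets an open question at visits.

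If the events on the common form are then counted by arm, the difference mixes two things: any effect of VR, and the difference in asking. The count alone cannot separate them. Section 4.3 also asks for causality to be assessed, and that judgement would have no control rate obtained by the same method to lean on.

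The timing matters. A later analysis plan can choose how to tabulate what was collected, but it cannot recover control-arm symptom data that nobody asked for.

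**Working it through.** The protocol gives no symptom rate, so there is no figure of its own to reproduce. The check counts enquiries and then shows what the counts imply under a labelled assumption.

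**Inputs**

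- Sessions per VR participant: 4 weeks × 3 per week = 12 (Section 3.6.2).
- Enquiries in the VR arm only: 12 before and 12 after sessions (Section 3.12).
- Enquiries in both arms after baseline (Section 4.3, visit undefined): 1 if counting stops at T1; 2 with T1 and T2 (Section 3.1); 4 with T1 plus the 1-, 2- and 3-month assessments named in the Discussion.
- Participants: 36 per arm (Section 3.4).
- Probability q that one enquiry yields a background symptom report: **not in the documents**. It is assumed equal in both arms and for every enquiry, with no VR effect, and is shown from 1% to 10%.

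**Enquiry counts.** Counting only the post-session checklists plus visits, which is the smaller imbalance, VR vs control is:

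- by T1: 12 + 1 = 13 vs 1;
- T1 and T2: 12 + 2 = 14 vs 2;
- T1 and 1, 2, 3 months: 12 + 4 = 16 vs 4.

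**Participants with at least one report.** If enquiries are independent, P = 1 − (1 − q)^k for k enquiries.

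| q | 13 vs 1 | 14 vs 2 | 16 vs 4 |
|---|---|---|---|
| 1% | 12% vs 1% | 13% vs 2% | 15% vs 4% |
| 2% | 23% vs 2% | 25% vs 4% | 28% vs 8% |
| 5% | 49% vs 5% | 51% vs 10% | 56% vs 19% |
| 10% | 75% vs 10% | 77% vs 19% | 81% vs 34% |

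At q = 5%: 1 − 0.95^13 = 0.487 against 0.05, and 1 − 0.95^16 = 0.560 against 1 − 0.95^4 = 0.185. With 36 per arm this is about 18 vs 2 participants by T1, and about 20 vs 7 through follow-up.

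**Adding the pre-session questions** gives 24 + 1 = 25 vs 1 by T1, or 72% vs 5% at q = 5%. Through follow-up it gives 24 + 4 = 28 vs 4, or 76% vs 19%.

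**Where the gap shrinks**

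- Persistent symptoms: if a participant either has the symptom at every enquiry or never has it, P = q in both arms and the gap in participants disappears.
- Recall: a T1 question that captured everything felt over the preceding four weeks would have a higher q than a question about one session, so the control figure by T1 would rise.
- Ward detection: symptoms noted in routine care would add reports in both arms, including among controls between T0 and T1, where the table assumes none.

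The table is therefore an illustration of direction and possible size, not a forecast.

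**The case against.** The strongest reply is that the protocol plans no comparison of adverse events by arm. The objectives, outcomes and statistical analysis contain none, and how safety data are tabulated is commonly left to an analysis plan. That is correct. A reader might infer that a planned safety test is biased, or that the trial's main result is; the document supports neither. What remains is that events are collected in both randomized arms on one form, so a by-arm count is the natural way to read them, and the collection schedule has to be settled before that.

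Second, close observation during VR protects participants, and controls have no session to observe. This also stands. The session monitoring should stay; only its use in a between-arm count is in question.

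Third, controls are not unobserved. Section 3.6.1 gives both arms ward symptom monitoring and safety assessments, so it would be wrong to infer that nothing is detected in controls between T0 and T1. Because both arms receive this care and it is not described as a structured adverse-event enquiry, it dilutes the imbalance but does not remove it.

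Fourth, the form records onset time, and the pre-session answers offer a within-person reference, though a less structured one. Some separation is therefore possible, but the text does not provide for it.

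A reader might also argue that unequal asking undermines the description of the intervention as low-risk in Section 4.3. It does not. That phrase is an advance reason for having no independent monitoring committee, not a conclusion to be drawn from this trial's control rate.

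**Conclusion.** The point holds as one of safety interpretation. Study-specified symptom enquiry differs by arm in frequency and in structure, and the text states both procedures, so this is not a matter of detail left to a fuller document. Any by-arm count of non-serious symptoms is expected to be higher in the VR arm even if VR causes none of them.

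The direction follows from the enquiry counts. The size rests on an assumed q, the same q for every enquiry, independence within a participant, and no ward detection. At q = 5%, 49% vs 5% by T1 lies towards the upper end for post-session checklists alone, and 56% vs 19% comes from the most conservative visit count considered. Persistent symptoms or ward detection would bring both closer together. Serious adverse events depend much less on being asked. The primary outcome and the planned tests are not affected. This is a worthwhile, inexpensive improvement rather than a flaw in the main analysis.

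**What to change.** 1. Give the same structured symptom checklist to both arms at T0, T1 and T2, and add it as a row in Table 1.
2. State that any between-arm comparison of non-serious adverse events will use these visit checklists, with serious adverse events reported alongside.
3. Report session-elicited symptoms separately, as descriptive data for the VR arm, with the pre-session answers as a within-person reference. Keep them out of any between-arm count.

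The session monitoring in Section 3.12 stays as it is. The cost is a few extra minutes with an existing form at three existing visits, one table row and a short reporting statement. The remedy has a limit: it gives a like-for-like comparison at visits, but still no control rate for symptoms felt immediately after a session.

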## Background

1

Depressive disorder is a common mental health condition characterized by persistent low mood (World Health Organization, 2023), loss of interest, and reduced energy. The global burden of depression continues to rise, with more than 300 million individuals affected worldwide, leading to substantial impairment in quality of life and significant socioeconomic costs. Notably, the peak onset of depression occurs during late adolescence and early adulthood, making this population particularly vulnerable.

In China, rapid social changes have exposed adolescents to increasing academic pressure, social challenges, and developmental stressors, contributing to a rising prevalence of mental health problems (Wu et al., 2022). Adolescent depressive disorder presents with distinct clinical features, including emotional instability, irritability, and somatic complaints, and is often associated with a higher risk of impulsive behaviors and suicide. Importantly, adolescence represents a critical period of neurodevelopment, during which cognitive control, emotional regulation, and social cognition are not yet fully matured (Menculini et al., 2024). This developmental vulnerability may predispose adolescents to maladaptive cognitive patterns, such as negative automatic thoughts and rumination, which can exacerbate and maintain depressive symptoms (Nigg, 2017). In addition, emerging evidence (Zhao et al., 2023; Li X. et al., 2025), suggests that adolescents with depression frequently exhibit cognitive impairments, particularly in memory, executive function, and attention (Schumacher et al., 2024).

Current treatment strategies for adolescent depression primarily include pharmacotherapy and psychotherapy. While these approaches have demonstrated efficacy, pharmacological treatments may be associated with adverse effects, and psychotherapeutic interventions often face challenges related to limited accessibility, low adherence, and restricted therapeutic settings. Therefore, there is a need for innovative and engaging interventions that can enhance treatment effectiveness and patient participation.

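### VR symptoms are graded on a checklist only after each session, with no matching score beforehand, so post-session rates may overstate the symptoms that VR induces

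*Protocol article*

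**What the plan says.** Section 3.12 of the protocol article monitors VR-related effects, "including dizziness, nausea, headache, visual discomfort, eye strain, fatigue, and disorientation". It describes three enquiries around a session:

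- Before: "Before each VR session, participants will be asked about any physical discomfort that might affect their participation".
- During: "During the intervention, trained researchers will continuously observe participants for signs of cybersickness or other adverse reactions".
- After: "Immediately after each session, participants will be asked about the presence and severity of any VR-related symptoms using a structured symptom checklist", together with open-ended questions.

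Adverse events go on a case report form, "including symptom type, onset time, duration, severity, actions taken, and outcome". Section 4.3 adds that "AEs will be assessed for severity, causality, and expectedness", without saying how causality is judged, and provides a general question on discomfort at each visit.

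Two other places bear on background symptoms. Section 1 names reduced energy as a feature of depressive disorder, and describes the adolescent form as having "distinct clinical features, including emotional instability, irritability, and somatic complaints". Section 3.3.1 requires stable drug treatment at entry, and section 3.6.1 lets the attending psychiatrist adjust it during the study.

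**The concern.** Several of the listed symptoms, fatigue and headache above all, are plausible in these participants without any headset. To tell a symptom that VR induced from one already there, the same items need to be graded on both sides of the session. The article describes a graded checklist on one side only. The pre-session enquiry has a threshold, namely whether the discomfort might affect taking part. A mild headache that would not stop anyone can pass below it and still be ticked 25 minutes later. Worsening of a symptom already present cannot be graded either.

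What is at stake is how the trial describes VR tolerability: how often sessions bring on symptoms, and how severe these are. The session records are the most direct evidence the trial will have on this, and section 4.3 gives the low risk of the intervention as a reason for having no independent data monitoring committee. A comparison of arms cannot fill the gap, because controls have no sessions and no session checklist is described for them. A single record at T0 would not serve well, since drug treatment may change over the 12 sessions.

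**Working it through.** **Step 1. Set the two instruments side by side (section 3.12).**

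| | Before the session | After the session |
|---|---|---|
| Scope | Any physical discomfort | VR-related symptoms |
| Threshold | Might affect taking part | None stated |
| Format | A question; no checklist stated | Structured checklist plus open-ended questions |
| Severity | No grade stated | Graded |

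The pre-session enquiry is narrower in threshold but not clearly narrower in content. What is missing is a common item list and a common grade, so no pre-to-post difference can be formed from the checklist.

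**Step 2. The plan's own figures.** The documents state no rate of VR symptoms, so there is no figure to reproduce. The only counts available are 36 per group (section 3.4) and 4 weeks × 3 sessions = 12 sessions (section 3.6.2). That gives at most 36 × 12 = 432 post-session checklists.

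**Step 3. Upper-bound illustration.** Both inputs are assumptions:

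- b = share of sessions that begin with at least one checklist symptom already present;
- v = share of symptom-free sessions in which VR induces one.

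If every pre-existing symptom persists and is ticked, then

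- checklist-positive share = b + (1 − b)v;
- newly induced share of all sessions = (1 − b)v;
- pre-existing share of positives = b / [b + (1 − b)v].

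| b | v | Positive | Newly induced | Pre-existing share of positives |
|---|---|---|---|---|
| 5% | 10% | 14.5% | 9.5% | 34% |
| 10% | 5% | 14.5% | 4.5% | 69% |
| 10% | 10% | 19% | 9% | 53% |
| 20% | 10% | 28% | 8% | 71% |
| 30% | 10% | 37% | 7% | 81% |
| 40% | 5% | 43% | 3% | 93% |
| 40% | 10% | 46% | 6% | 87% |

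At b = 20% and v = 10%, 432 × 0.28 = 121 checklists would be positive, of which 432 × 0.20 = 86 began with a symptom.

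**Step 4. Allow the existing safeguards to work.** Let k be the fraction of pre-existing symptoms still recorded as VR-related after the participant's own judgement, onset time and causality review. The recorded share becomes kb + (1 − b)v. At b = 20% and v = 10%:

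- k = 1: 0.20 + 0.08 = 28%;
- k = 0.5: 0.10 + 0.08 = 18%;
- k = 0: 8%, with no overstatement in this model.

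The documents give no way to know k, so the size of the overstatement is unknown and could be nil.

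**Limit of the model.** A session in which VR worsens an existing symptom, or adds a second one, counts here as pre-existing. The last column is therefore not the complement of the VR effect. Only a score before and after would separate these sessions.

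**The case against.** A reader might infer that the method captures symptom prevalence after a session instead of symptoms caused by VR, that the causality grading has no baseline at all, and that the reported rate is bound to be too high. The documents do not support any of these:

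- The post-session question is worded as being about VR-related symptoms, and open-ended questions accompany it.
- Trained researchers watch throughout the session.
- The case report form holds onset time and duration, the fields that separate an earlier symptom from a new one.
- The pre-session enquiry gives some baseline, and section 4.3 requires a causality assessment.

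It can also be said that no objective, outcome or analysis names a rate of VR-induced symptoms, that section 3.12 exists chiefly to protect participants, that over-recording harm errs on the cautious side, and that a condensed article may leave form content to documents not shown.

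Much of this stands. It removes the stronger reading and makes the figures above a worst case. It does not remove the mismatch. The VR-related wording asks unblinded adolescents to judge cause for themselves. Onset of a mild subjective symptom rests on recall. Observation sees signs better than it sees headache, eye strain or fatigue. The article is not merely silent: it describes both enquiries, and as described they differ. If a fuller document already specifies a matched pre-session checklist, the point falls.

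**Conclusion.** The point holds in a limited form. As the article describes it, a graded checklist is given only after each session, so attribution to VR depends on participant judgement, recalled onset, observation and an unspecified causality review. Post-session checklist rates may overstate VR-induced symptoms by an unknown amount.

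No size can be taken from the documents. With b from 10% to 40% and v from 5% to 10%, the raw rate would be at most 14.5% to 46%, against 3% to 9% newly induced. These are upper bounds: they assume that every pre-existing symptom persists, is ticked as VR-related and survives review. The issue concerns the description of tolerability within the VR arm. The primary outcome, the secondary outcomes and the sample size are untouched. It is a cheap improvement to safety data collection, not an error that threatens the trial's main result.

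**What to change.** Give the same structured checklist, with the same items and severity grades, immediately before and immediately after every VR session. Count a symptom as arising with the session if it is new, or at least one grade worse, after it. Report that count alongside the raw post-session count, and state that the causality assessment in section 4.3 uses the pre-session score.

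The cost is an estimated one minute per session, or about 12 minutes per VR participant over 12 sessions, using an existing form and a researcher already present. The downside is slightly more burden and some risk that asking beforehand prompts symptoms. The change should be made before sessions begin, because a missing pre-session score cannot be recovered later. No change to the suspension or termination rules is proposed.

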## Ethics and dissemination

4

### Ethics approval

4.1

This study has been approved by the Institutional Review Board of Xinxiang Medical University (Approval No. XYLL-20250494) and the Ethics Committee of the Second Affiliated Hospital of Xinxiang Medical University (Approval No. XYEFYLL-(Research)-2025–116). Any protocol amendments will be submitted to both ethics committees for approval prior to implementation.

### Informed consent

4.2

Trained research staff will obtain written informed consent from both the participants and their legal guardians after providing a thorough explanation of the study’s purpose, procedures, potential risks, and benefits. Consent will be obtained before any study-related procedures are performed. The informed consent form is provided as Supplementary File 1.

### Safety monitoring and adverse events

4.3

All adverse events (AEs) and serious adverse events (SAEs) will be recorded from enrolment through the follow-up period. Participants will be asked at each visit about any discomfort or unexpected symptoms. AEs will be assessed for severity, causality, and expectedness. SAEs will be reported to the ethics committees and the sponsor within 24 h. The principal investigator is responsible for managing AEs and ensuring participant safety. No independent data monitoring committee was established, as the trial involves a low-risk, short-term intervention and is monitored jointly by the investigators and the institutional ethics committees.

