#### Control group

3.6.1

Participants in the control group will receive standard inpatient psychiatric care as provided by the Department of Child and Adolescent Psychiatry. Standard care includes pharmacological treatment prescribed by the attending psychiatrist, routine nursing care, symptom monitoring, safety assessments, medication management, and supportive communication as part of usual inpatient care. Pharmacological treatment will be adjusted by the attending psychiatrist based on clinical needs and will not be influenced by the research team.

Supportive communication is routinely provided by psychiatrists and psychiatric nurses during daily clinical interactions, with an emphasis on emotional support, treatment adherence, encouragement of coping skills, and risk assessment. However, participants will not receive any structured psychological therapy during the study period. To minimize potential confounding factors, both groups will receive the same standard inpatient psychiatric care throughout the study. The only difference between the two groups is that participants in the intervention group will additionally receive a virtual reality-based intervention. Standardized case report forms will be used to document medication use, medication adjustments, psychiatric consultations, and other clinically relevant interventions during the study period in order to monitor treatment exposure and potential co-interventions.

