### Outcomes

3.7

The primary outcome of this study is the change in the 24-item Hamilton Depression Rating Scale (HAMD-24) (Wiebe et al., 2022) score from baseline (T0) to post-intervention (T1). Assessments will be conducted by trained evaluators who are blinded to group allocation.

Secondary outcomes include: 1. Anxiety symptoms, assessed using the Hamilton Anxiety Rating Scale-14 (HAMA-14) (Li Y. et al., 2025); 2. Self-reported depressive symptoms (Li X. et al., 2025), assessed using the Children’s Depression Inventory (CDI); 3. Cognitive function (Jia et al., 2021), assessed using the Montreal Cognitive Assessment (MoCA). All psychological assessments will be conducted at baseline (T0), post-intervention (T1), and follow-up (T2). 4. Heart rate variability (HRV) parameters (Shapiro et al., 2007; Kircanski et al., 2019), including SDNN, RMSSD, low-frequency power (LF), high-frequency power (HF), and the LF/HF ratio, will be measured as objective physiological outcomes. Electrocardiogram signals will be recorded for at least 5 min under resting conditions in a quiet environment, and both time-domain and frequency-domain analyses will be performed.

Although the HAMD was originally developed for adults, it has been widely used in clinical studies involving adolescents with major depressive disorder and has demonstrated acceptable reliability and validity in adolescent populations (Zhao et al., 2023). Previous studies have shown that HAMD scores are significantly correlated with other well-established measures of depression severity in adolescents, supporting its clinical utility in assessing symptom severity and treatment response (Croarkin et al., 2021; Li et al., 2023). The HAMD is routinely used in psychiatric clinical practice, and our team has extensive experience in its administration. The scale has good sensitivity to symptom change and facilitates comparisons with previous depression trials. To enhance the assessment of depressive symptoms and address potential developmental limitations, the CDI—a developmentally appropriate self-report measure for children and adolescents—will also be administered at all assessment time points. The combined use of a clinician-rated scale and a self-report measure is expected to provide a more comprehensive assessment of the severity of depressive symptoms.

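### Symptom enquiry is more frequent in the VR arm, and after discharge the only safety enquiry described is a general question that names neither suicidal ideation nor self-harm

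*Protocol article*

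**What the plan says.** The Protocol article describes safety enquiry in two sections.

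- **Section 4.3, both arms.** Adverse events and serious adverse events "will be recorded from enrolment through the follow-up period". The method of enquiry is: "Participants will be asked at each visit about any discomfort or unexpected symptoms".
- **Section 3.12, VR sessions only.** There is a question about physical discomfort before each session and observation during it. Immediately afterwards, "participants will be asked about the presence and severity of any VR-related symptoms using a structured symptom checklist and open-ended questions". The section then states: "All adverse events will be recorded in a standardized case report form".

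Section 3.6.2 has the VR programme "delivered over a period of 4 weeks, with three sessions per week". Section 3.6.1 describes usual care, which covers safety assessments and daily supportive contact "with an emphasis on emotional support, treatment adherence, encouragement of coping skills, and risk assessment". It adds that "both groups will receive the same standard inpatient psychiatric care throughout the study".

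The Discussion places the follow-up assessments one, two and three months after discharge. The Background says that adolescent depression often carries a raised risk of suicide. Neither safety section mentions suicidal ideation or self-harm.

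**The concern.** Two things are at stake.

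The first is comparability. An adverse event enters the record only if someone observes it or asks about it. Several items on the VR symptom list, such as headache, nausea, dizziness and fatigue, are not specific to a headset, and a control participant on medication may have them too. If symptoms found by the session checklist are counted together with events found by the shared visit question, the VR arm can show more adverse events simply because it was asked more often.

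The second is participant safety after discharge. An adolescent asked about discomfort or unexpected symptoms may not volunteer suicidal thoughts or self-harm. Such events could then be missed or recognised late, in a period when ward staff no longer see the participant every day.

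**Working it through.** There is no figure in the plan to reproduce here. The check is a count of enquiry occasions and a comparison of sections.

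**1. Enquiry occasions per participant.**

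- Shared general question (4.3): once per visit. Table 1 shows T0, T1 and a single T2, so 3 occasions. If follow-up is the three monthly contacts in the Discussion, T0 + T1 + 3 = 5.
- Post-session checklist with open-ended questions (3.12 and 3.6.2): 4 weeks × 3 sessions = 12 in the VR arm if all sessions are attended, and 0 in the control arm, which has no sessions.
- Totals: control 3 or 5; VR 3 + 12 = 15 or 5 + 12 = 17.

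The pre-session question is left out because it concerns fitness for the session. Ward monitoring is left out because it is common to both arms and its frequency is not given. For that reason the totals should not be turned into a ratio of detection.

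**2. Where the answers go.** Section 3.12 puts every adverse event on a standardized form with symptom type, onset time, duration, severity, action and outcome. Section 4.3 adds causality and expectedness. How the event was found is not among the listed items. Onset time and causality would help to separate session symptoms, but the text does not say that they will be separated.

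**3. Enquiry by period.**

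| Period | Both arms | VR arm only |
|---|---|---|
| Inpatient, during the 4-week course | General visit question; ward safety and risk assessment | Session questions, observation and checklist |
| After discharge | General visit question | None |

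Section 3.6.1 says that the shared care lasts for the whole study. It is defined as inpatient care, however, and its risk assessment takes place in daily clinical contact. It cannot extend to contacts that the Discussion dates from discharge. For those contacts the general question is the only safety enquiry left in the text.

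**4. Whether the outcome scales fill the gap.** Section 3.7 and Table 1 give HAMD-24 and CDI in both arms at T0, T1 and T2. The article presents them as efficacy measures, does not list their items, and describes no step from a worrying answer to the treating team. They may cover suicidality at T2, but the article does not settle it.

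**The case against.** The strongest reply has four parts.

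- **The checklist is proper tolerability monitoring.** It targets VR-related symptoms and supports the rule for stopping a session. Controls have no headset exposure to be asked about. This stands, and the checklist should stay.
- **No between-arm comparison of adverse events is planned.** Safety is not among the objectives (section 2), the outcomes (3.7) or the analyses (3.11), and nothing says that the two sources will be pooled. This also stands. The concern applies to any by-arm table that pools them; it does not show that a biased analysis has been specified.
- **This is a condensed article.** Suicide-risk questions may be in the full protocol and table layout in the analysis plan. This stands in part. However, the article sets out timing, instruments, form fields, stopping rules and reporting times in two sections, so the scheme as stated can be judged.
- **The general question is broad.** Serious events are reported within 24 hours and the principal investigator is responsible for safety. That governs events once they are known. It does not bring unvolunteered ideation to light.

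A reader might infer that controls receive less suicide-risk assessment than VR participants. The documents do not support this: both arms have the same inpatient care, including risk assessment, and the session checklist concerns VR symptoms. A reader might also infer that suicidality goes unassessed after discharge. That is not shown either, because HAMD-24 and CDI at T2 may cover it.

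**Conclusion.** The point holds in two limited respects, as something for the sponsor to consider.

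1. The trial's own symptom enquiry is unequal by arm: 12 extra post-session enquiries per VR participant with full attendance, against none per control, on top of a visit question that both share. By-arm counts pooling the two sources would partly measure frequency of asking.
2. After discharge, the only safety enquiry described names neither suicidal ideation nor self-harm, in a population whose suicide risk the article itself acknowledges, and no referral step from the depression scales is described.

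The count of 12 measures opportunity to report. It does not measure events missed or counted in excess, and the documents give no event or detection rates from which to estimate either. The second part rests on reading section 3.6.1's risk assessment as ending at discharge, and on the full protocol adding nothing to section 4.3. The sample size and the primary analysis are unaffected. Confidence is medium, because the full protocol is not shown.

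**What to change.** In section 4.3:

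- Add one question on suicidal ideation or behaviour and self-harm, worded identically in both arms, at each existing post-discharge contact. Ask it after the blinded ratings are complete, so that the answer cannot influence them.
- Refer positive answers, including any on suicide items in the HAMD-24 or CDI versions used, to the principal investigator and the treating team the same day.
- Keep the VR checklist for tolerability. Report its symptoms separately from adverse events elicited by the question common to both arms, and keep by-arm adverse-event tables descriptive.
- If the full protocol already contains such a question and referral step, one sentence saying so is enough for that part.

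The cost is a wording change, one added question per follow-up contact, a split table, and brief instruction to raters on referral, including how to reach the treating team for a discharged participant. No new visit is needed. The downside is slightly longer follow-up contacts and a few more events to record and refer.
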